Poor adherence to clinical guidelines is not unique to Spain. In the year 2007, a similar problem was identified in the United Kingdom, ultimately leading to the development of a program entitled “IAPT” designed to promote the treatment of EDs in PC with CBT in accordance with the NICE recommendations (NICE, 2011). That initiative has been very successful, resulting in substantially improved treatment outcomes while simultaneously reducing costs (particularly due to decreased drug prescriptions) compared to the usual PC treatment (Radhakrishnan et al., 2013). Indeed, given the success of the IAPT program with EDs, the program has been extended for use in children and in patients with chronic physical conditions (Gyani et al., 2013). Due to the considerable savings of the CBT approach versus drug-based therapies, one recent study estimated that even if the number of patients treated with CBT in the PC setting doubled (from 500,000 to 1 million per year), the net cost would likely be zero if patients with common mental disorders (anxiety and depression) and those with comorbid chronic physical conditions receive CBT (Layard and Clark, 2015).

In Spain, a randomized controlled clinical trial [the Psychology in Primary Care (PsicAP) study] is currently in progress to compare evidence-based psychological techniques [such as transdiagnostic (TD)-CBT] to treatment-as-usual (TAU) (Cano-Vindel et al., 2016) in patients with EDs. Given this context, the present work describes the design of a study being conducted as part of the PsicAP clinical trial (sub-study 2). The aim of this sub-study is to assess and compare the costs associated with psychological and pharmacological treatment approaches for mental disorders in the PC setting in Spain. This study will assess the relationship between cost-effectiveness and cost-utility of these two different treatment approaches. We hypothesize that the costs of switching from TAU to a group-based TD-CBT approach will be justified by the expected additional clinical and social benefits (a superiority trial).

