### Sample Size

Two programs were used to determine sample size: (a) G^∗^Power3 (Faul et al., 2007) which prioritizes statistical power, and (b) SSS-CET (Software for Sample Sizes in Cost Effectiveness Trials) which uses a Bayesian approach (Sarker et al., 2013). Based on these analyses, a sample size of 176 participants per group was established (*N* = 352). However, it should be noted that previous investigations have proven that 150 participants are sufficient for a cost-effectiveness study (Rubio-Valera et al., 2013, 2015). Thus, the sample size established for this study is 150 participants per study group (*n* = 300).

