#### Description of Cost Analysis

Direct costs of health care will be estimated by adding the costs derived from medication use (antidepressants, hypnotics, sedatives, and anxiolytics), medical tests, use of health-related services, and staffing costs. The cost of medications will be calculated by determining the price per milligram (mg) during the study period according to the Vademecum International (Vidal, 2014), including value-added tax. Total costs of medications will be calculated by multiplying the price per mg by the daily dose (mg) and the number of days of drug treatment.

The main source of unit cost data related to public medical tests and use of health services will be obtained from the fee information published by the Official Government Journal of the Autonomous Community of Madrid (2013). Indirect costs will be calculated according to the number of days on sick leave multiplied by the minimum daily wage in Spain for 2015 (€21.62). Finally, total costs will be calculated by summing the total direct and indirect costs. The unit costs will be expressed in Euros (€) based on 2015 prices.

Currently, there is no reference fee for the TD-CBT intervention that will be used with the experimental group. The estimated cost of a consultation with a public sector GP in Spain is €39 (not including complementary tests). Given that salaries for psychologists in Spain are similar to those of GPs, we will use this amount (€39) to calculate the cost of the TD-CBT intervention (i.e., €39 multiplied by the number of assessment and treatment sessions, €39 × 9 = €351). Since the GP consultation fees are understood to include the cost of office space, we will not add any additional costs for office rent to the cost of the therapy. Accordingly, the total cost of the evaluation and psychological intervention (nine sessions) per person is estimated at €43.87 (€351/8).

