#### Cost-Effectiveness Analysis

The cost-effectiveness analysis will be carried out by calculating the incremental cost-effectiveness ratios (ICER), defined as the difference in mean costs divided by the increase in effectiveness of the various therapeutic alternatives.

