#### Cost-Utility Analysis

Cost-utility analysis is a method of economic evaluation based on preferences or utilities rated by individuals; in other words, the value that an individual assigns to their health status. Thus, the economic evaluation depends on the social perspective of the individual, in which patients express preferences about their health. The EuroQoL-5D Questionnaire (EQ-5D – Spanish version) will be used for the cost-utility analysis. This is a generic QOL instrument consisting of five domains, as follows: mobility; anxiety/depression; pain/discomfort; daily activities; and self-care. These five domains are coded into five severity levels, as follows: no problems; slight problems; moderate problems; severe problems; extreme problems. In this way, 3125 distinct health states can be established. Health states enable us to obtain a population-based preference score per country (the EQ-5D index). The assigned values range from 0 (death) to 1 (perfect health). In addition, this index includes a VAS similar to a thermometer, which measures health from 0 (worst imaginable health state) to 100 (best imaginable health state) (Rabin et al., 2015).

Through the EQ-5D health questionnaire, we will calculate utility as QALYs using the Spanish fees described above.

Using these data, we will calculate the incremental cost-utility ratios, defined as the difference in mean costs divided by the difference in mean QALYS. Given that the duration of this study is only 12 months, neither costs nor outcomes are subject to discount. To obtain more precise cost-utility ratios, these ratios will be calculated by means of the bootstrapping method (a resampling method), which involves creating a large number of samples with replacement from the original sample data, thus allowing for a distribution that better resembles the actual distribution of the population from which the original data was drawn. In this way, the study will generate 1000 random samples which will be used to define the confidence intervals for the cost-utility ratios.

Missing-data analysis will be computed using Student’s *t*-test and chi-square tests. Variables included in the analysis will be severity level, gender, and age; this will allow us to ascertain whether unexpected missing data due to participant dropout are related to chance or not.

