If our hypothesis—that the costs of switching from TAU to a group TD-CBT approach is justified by the clinical and social benefits—is confirmed, this could have a profound impact on the treatment of EDs in the PC setting in Spain. Considering that EDs affect nearly one-third of PC patients, this would have important implications, as evidence-based interventions recommended by clinical practice guidelines should lead to better outcomes and improved QOL in our patients. Moreover, if our expected results are achieved, it would be possible to significantly reduce the cost of treating these disorders—currently, 2.2% of GDP in our country—by replacing pharmacotherapy with group-based CBT interventions in this patient population.

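### The bootstrap interval is placed on the cost-utility ratio, which by itself cannot tell whether group therapy is dominant or dominated

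*Protocol article*

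**What the plan says.** The Cost-Utility Analysis section of the protocol article defines the incremental cost-utility ratio as a quotient, "defined as the difference in mean costs divided by the difference in mean QALYS". It then names the bootstrap as the method of inference: "the study will generate 1000 random samples which will be used to define the confidence intervals for the cost-utility ratios". No other inferential procedure is stated for the economic comparison. The Cost-Effectiveness Analysis section gives only a point definition of its ratio, "defined as the difference in mean costs divided by the increase in effectiveness of the various therapeutic alternatives". The Sensitivity Analysis section is a single general sentence.

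The hypothesis that these analyses serve is in the Introduction, where it is called a superiority question: "We hypothesize that the costs of switching from TAU to a group-based TD-CBT approach will be justified by the expected additional clinical and social benefits". The Discussion goes further and says that, if the expected results are achieved, "it would be possible to significantly reduce the cost of treating these disorders". The Sample Size section fixes 150 participants per group.

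**The concern.** A ratio of two differences discards their signs. A negative value can mean that TD-CBT saves money and improves health, or that it costs more and worsens health. A positive value can mean paying more for more health, or saving money at the price of health. An interval for the ratio inherits this ambiguity.

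Two further problems follow.

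- **Lost ordering.** Where TD-CBT is cheaper and better, the size of the ratio no longer ranks value for money. A saving of €300 with a gain of 0.03 QALY gives -10,000. The same saving with a gain of 0.06 QALY, which is plainly better, gives -5,000.
- **Discontinuity.** As the QALY difference passes through zero, the ratio jumps from very large values of one sign to very large values of the other. If some resamples fall on each side of zero, the percentile limits no longer bracket a coherent set of values.

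The Discussion foresees savings together with better outcomes, so this region is plausible. At stake is whether the one interval reported for the economic result can be read at all.

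**Working it through.** The plan states no numerical result on this point, so there is none to reproduce. The check has an algebraic part, which needs no assumptions, and an illustration, which does.

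**Algebra.** Write ΔC for the difference in mean cost and ΔQ for the difference in mean QALYs, TD-CBT minus treatment as usual. The ratio is R = ΔC/ΔQ, and (-ΔC)/(-ΔQ) = ΔC/ΔQ. Hence:

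- cheaper and better: -300/+0.03 = -€10,000 per QALY
- dearer and worse: +300/-0.03 = -€10,000 per QALY
- dearer and better: +300/+0.03 = +€10,000 per QALY
- cheaper and worse: -300/-0.03 = +€10,000 per QALY

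**Inputs for the illustration.** From the protocol article: 150 per arm. Assumed, because the article gives no such figures: cost SD €1,000; QALY SD 0.05, 0.10 or 0.20; differences of ±0.03 QALY and ∓€100; cost and QALY differences uncorrelated and normal; willingness to pay (λ) €25,000 per QALY.

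**Standard errors.** SE = SD × √(2/150) = SD × 0.1155. This gives €115.5 for cost, and 0.0058, 0.0115 and 0.0231 for QALYs.

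**Interval on the ratio** (2.5th and 97.5th percentiles of ΔC/ΔQ, by simulation):

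| QALY SD | Cheaper and better (-€100, +0.03) | Dearer and worse (+€100, -0.03) | Draws in which ΔQ changes sign |
|---|---|---|---|
| 0.05 | -12,200 to +4,400 | -12,200 to +4,400 | essentially none |
| 0.10 | -19,000 to +5,400 | -19,100 to +5,400 | 0.5% |
| 0.20 | -41,600 to +32,100 | -41,700 to +31,800 | 9.7% |

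The two middle columns differ only by simulation noise.

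**Net monetary benefit for the same inputs.** NMB = λΔQ - ΔC, with SE = √[(λ × SE of ΔQ)² + (SE of ΔC)²].

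- Cheaper and better: 25,000 × 0.03 + 100 = +€850
- Dearer and worse: 25,000 × (-0.03) - 100 = -€850

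| QALY SD | SE of NMB | 95% CI, cheaper and better | 95% CI, dearer and worse | P(NMB > 0) |
|---|---|---|---|---|
| 0.05 | √(144.3² + 115.5²) = 184.8 | +488 to +1,212 | -1,212 to -488 | >0.99 v <0.01 |
| 0.10 | √(288.7² + 115.5²) = 310.9 | +241 to +1,459 | -1,459 to -241 | 0.997 v 0.003 |
| 0.20 | √(577.4² + 115.5²) = 588.8 | -304 to +2,004 | -2,004 to +304 | 0.93 v 0.07 |

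At the largest SD neither net benefit interval excludes zero, but each still points in the right direction.

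**A tidy interval can mislead too.** This case used an actual bootstrap with 1000 resamples, 150 per arm, assumed SDs of €1,000 and 0.10, and differences of ±0.03 QALY and ∓€300. The cheaper and better case gave -38,906 to -2,472, with 99.1% of resamples in that quadrant. The dearer and worse case gave -40,746 to -2,178, with 98.5% in the opposite quadrant. Both intervals lie wholly below zero and look alike. At an assumed €20,000 per QALY, net benefit from those resamples was +€900 (95% CI +432 to +1,406) against -€900 (-1,388 to -387).

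**The case against.** A reader might infer that the hypothesis cannot be tested at all. The documents do not support that. Both mean differences, with their signs, must be computed before the ratio exists. Each of the 1000 resamples yields a cost difference and a QALY difference, so the planned bootstrap already holds the information that separates the cases. The hypothesis also rests on clinical benefit: symptoms are among the main outcomes, and the article has a separate section on clinical effectiveness.

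A reader might also count as errors the absence of a willingness-to-pay value, of a decision rule, and of an interval for the cost-effectiveness ratio. A journal article can leave these to a fuller protocol or analysis plan that is not shown, so they are not held against it. The choice of the ratio as the quantity given an interval is different. The article states it, and a later plan would have to replace it, not merely add to it.

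Two further objections stand in part. The hypothesis speaks of costs being justified, which suggests paying more for more health, where a ratio is easier to interpret. The saving in the Discussion is conditional and concerns the national cost of these disorders. It shows that the cheaper and better case is foreseen, not that it is the planned scenario. Second, the width of the interval depends on the assumed inputs. With +0.06 QALY, +€100 and a QALY SD of 0.20, the interval is about -2,700 to +9,600, and the QALY difference changes sign in only about 0.5% of draws. An unreadable result is therefore a possibility, not a certainty. The sign ambiguity does not depend on these inputs.

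**Conclusion.** The concern holds for the interval on the cost-utility ratio. As specified, that interval cannot by itself support or refute the hypothesis, because opposite conclusions give the same ratio and, in every scenario run, virtually the same interval. This follows from algebra.

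The size of the instability near a zero QALY difference rests on assumed SDs and differences. Over QALY SDs of 0.05 to 0.20, the width of the ratio interval grows from about 16,600 to about 73,700 euros per QALY (4,400 + 12,200; 32,100 + 41,600), while net benefit stays at +€850 or -€850 according to the case. The €25,000 and €20,000 values are assumptions for illustration and are not proposed as Spanish thresholds.

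**What to change.** Keep the 1000 resamples and change what is computed from them. Give bootstrap 95% intervals for the mean cost difference, the mean QALY difference and the incremental net monetary benefit over a pre-stated willingness-to-pay range. Show the cost-effectiveness plane and the acceptability curve from the same resamples. Report the cost-utility ratio as a point estimate, and only when neither arm dominates. Any interpretation of whether costs are justified should then refer to net benefit or to the joint cost and QALY differences.

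The change is one of wording and programming. It needs no new patients, data or resamples. The one small cost is that a willingness-to-pay range has to be chosen and stated before the results are seen.

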#### Retention

If necessary, we will send the participant a link by email to enable the patient to complete the computerized measures at home. Patients are contacted by phone to encourage completion of the questionnaires. Patients who discontinue or drop out of treatment will still be invited to complete the post-treatment follow-up assessments, particularly the first post-treatment assessment.

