### Statistical Analysis

#### Analysis of Clinical Effectiveness

This study will be conducted on an intention-to-treat basis. Both groups will be compared to verify that there are no significant between-group differences at baseline. For comparisons, the ANOVA method will be used for continuous variables and the Chi-square test for categorical variables. Subsequently, a repeated measurement of ANOVA, including all variables over time, will be performed to assess whether missing values respond to a random or non-random pattern. If the missing values are greater than 5% the Expectation Maximization (EM) will be used as a data imputation method, as recommended by the literature (Schlomer et al., 2010).

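### The cost-utility drop-out check omits treatment arm, so it cannot show whether drop-out is by chance in the sense that matters for a between-arm contrast

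*Protocol article*

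**What the plan says.** The last paragraph of Cost-Utility Analysis fixes three things.

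- The tests: "Missing-data analysis will be computed using Student’s *t*-test and chi-square tests".
- The variables: "Variables included in the analysis will be severity level, gender, and age; this will allow us to ascertain whether unexpected missing data". Treatment arm is not among them, and no within-arm comparison or interaction is mentioned.
- The conclusion to be drawn: whether missing data "due to participant dropout are related to chance or not".

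The same section defines the result as a ratio of two between-arm differences: "defined as the difference in mean costs divided by the difference in mean QALYS". Sample Size sets the numbers: "Thus, the sample size established for this study is 150 participants per study group".

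Other sections touch on missing data without settling this point.

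- Analysis of Clinical Effectiveness has a separate pattern check, a repeated-measures ANOVA "including all variables over time, will be performed to assess whether missing values respond to a random or non-random pattern". It also has EM imputation once more than 5% of values are missing. That section concerns clinical outcomes, and its check does not name arm.
- Sensitivity Analysis names no drop-out scenario.
- Retention expects treatment drop-outs: "Patients who discontinue or drop out of treatment will still be invited to complete the post-treatment follow-up assessments".

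**The concern.** The cost-utility result is a difference between arms. Drop-out that depends on prognosis in the same way in both arms does little harm to a difference. Drop-out that depends on prognosis differently by arm can distort it. A comparison of drop-outs with completers that ignores arm answers a different question: whether, averaged over both arms, the two groups are alike in severity, gender and age. If more severe patients leave one arm and milder patients leave the other, the averages can agree and the check reads as chance.

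The interventions give drop-out room to differ. TD-CBT asks for seven 1.5-hour group sessions over 24 weeks, while the control arm continues with usual GP care. Follow-up in both arms runs to 12 months after treatment. The article gives no expected drop-out rate or pattern. At stake is whether a non-significant check is taken as reassurance about the incremental cost and QALY.

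**Working it through.** The plan gives no figure to reproduce, so the check is of the mechanism.

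**Inputs.** From the article: 150 per arm and the three listed variables. Assumed, because the article gives none: drop-out of 20% in each arm (or 30% in TD-CBT and 10% in TAU), two-sided 5% per test, a correlation of 0.5 between baseline severity and outcome, no true treatment effect, and pooling over arms. Severity has SD 1 and is tested with a t-test. Drop-out is logistic in severity, with log-odds slope b1 in TD-CBT and b0 in TAU. Rates are at mean severity.

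**What the pooled test measures.** To first order, drop-outs in an arm with rate p and slope b have mean severity b(1 − p), and completers have −bp. With equal arms and equal p, the pooled difference between drop-outs and completers is (b1 + b0)/2, the average slope. Its standard error with 60 drop-outs and 240 completers is √(1/60 + 1/240) = 0.144.

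**What biases the contrast.** Completers' mean severity is shifted by −b1·p1 in TD-CBT and −b0·p0 in TAU. With correlation 0.5, the unadjusted completer difference is off by about 0.5 × |b1·p1 − b0·p0|. At equal p this depends on the difference of the slopes.

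The test therefore tracks the average slope and the bias tracks the difference. For opposite slopes of ±0.8:

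- test signal (0.8 − 0.8)/2 = 0
- bias 0.5 × 0.2 × 1.6 = 0.16 SD

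**Simulation set beside the formula** (repeat runs differ by a percentage point or two):

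| Drop-out TD-CBT / TAU | Slopes TD-CBT / TAU | Pooled severity test fires | Bias by formula (SD) |
|---|---|---|---|
| 20% / 20% | 0 / 0 | 5% | 0.00 |
| 30% / 10% | 0 / 0 | 5% | 0.00 |
| 20% / 20% | +0.5 / −0.5 | 5% | 0.10 |
| 20% / 20% | +0.8 / −0.8 | about 5% | 0.16 |
| 30% / 10% | +0.8 / −0.8 | about 34% | 0.5 × (0.24 + 0.08) = 0.16 |
| 20% / 20% | +0.8 / −0.3 | about 37% | 0.5 × 0.2 × 1.1 = 0.11 |
| 20% / 20% | +0.8 / 0 | about 76% | 0.5 × 0.2 × 0.8 = 0.08 |
| 20% / 20% | +0.5 / 0 | about 40% | 0.05 |

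Simulated biases agree with the formula to about 0.01 SD. The ±0.8 row at 20% gave up to 0.17 SD, with about 24% false positives for the unadjusted completer contrast.

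**Unequal rates alone.** In the 30% / 10% row with zero slopes, a chi-square of drop-out by arm fires in 99% of trials while the listed tests behave as under chance. The contrast is unbiased. The check misses non-chance drop-out there, but no harm follows.

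**What removes the bias.** Adding baseline severity to the outcome model brings the bias to 0.00–0.01 SD in every severity-driven pattern. It does not help when drop-out depends on unseen outcomes. With 10% drop-out in TAU and 30% outcome-related drop-out in TD-CBT, the bias is 0.20 SD before and after adjustment. The three listed tests flag 13.8% there, against 14.3% under pure chance.

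**The case against.** The case against is substantial, and several stronger readings that a reader might infer do not stand.

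- **The plan pools the arms.** It does not say so. Pooling is the natural reading of two-group tests with no arm variable. Stratification could be set out in a fuller plan that is not shown.
- **The plan analyses completers as a chance subset.** No section says this. The study is on an intention-to-treat basis, and no action is attached to the drop-out check. EM imputation is triggered by the amount missing, although its reach to costs and QALYs is unclear. The bias figures above are for an unadjusted completer contrast that the article never specifies.
- **Differential attrition in itself biases the result.** It does not when drop-out is random within arm; the figures above give zero.
- **The check is blind to arm-specific drop-out related to severity.** Only exact cancellation brings it down to 5%. In the less symmetric patterns with a 0.8 slope it fires in roughly a third to three quarters of trials, and nothing in the article suggests a crossed pattern.
- **The check raises a false alarm in about 15% of trials.** That needs a 5% level per test and an any-of-three rule, and the article states neither.

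It is also fair to say that protection comes from how missing costs and QALYs are handled, not from the variable list of a descriptive check. All of this limits the size of the point. What remains is a stated method tied to a stated conclusion that it cannot support, in the only missing-data paragraph written for the cost-utility analysis.

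**Conclusion.** The point holds in limited form. Tests on severity level, gender and age without treatment arm cannot ascertain whether drop-out is by chance for a between-arm contrast. On the pooled reading they respond to the average relation of severity to drop-out, whereas bias depends mainly on how that relation differs between arms.

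For the patterns with a 0.8 slope in TD-CBT, the severity test fires in about 5% of trials (exact opposition) to 77% (no slope in TAU). An unadjusted completer contrast would be off by about 0.17 down to 0.08 SD. These sizes rest on the assumed drop-out rates, slopes and 0.5 correlation. They cannot be turned into QALYs or euros, because the article gives no standard deviations. Independently of those assumptions, no comparison of baseline variables can prove chance when drop-out may depend on unseen outcomes. Importance is minor to moderate.

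**What to change.** In Cost-Utility Analysis:

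1. Report drop-out and missing cost and QALY data by arm.
2. Replace the marginal tests with a descriptive logistic model of missing cost/QALY data on arm, baseline severity, gender, age and baseline EQ-5D, with an arm-by-severity term. Arm as a main effect is not enough: in a crossed pattern with 20% drop-out per arm, drop-out by arm flags only 4.8%, about its chance rate.
3. Whatever the model's p-values, include arm and these baseline variables (at least severity and EQ-5D) in the imputation or adjusted analysis of costs and QALYs. This is the step that protects the result.
4. Delete the claim that the check ascertains whether drop-out is by chance.
5. Under Sensitivity Analysis, add a scenario for drop-out not at random.

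The cost is wording and a few lines of code on data already planned, with no extra patients or visits. The interaction term is imprecise when drop-out is low. It also gains power only where the slopes oppose. Its standard error at 20% drop-out is about √(2/(150 × 0.16)) = 0.289. For slopes +0.8 and 0 the signal is then 0.8/0.289 = 2.8 standard errors, the same as the pooled test's 0.40/0.144 = 2.8. For ±0.8 it is 1.6/0.289 = 5.5, against 0 for the pooled test.

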### Main Outcomes

The main outcomes are the clinical symptoms assessed by the PHQ: depression, anxiety, panic, and somatic symptoms, as well as economical variables and EuroQol 5D outcomes in terms of QALYs.

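### The clinical and cost-utility sections give different missing-data procedures, and it is not stated which one governs costs and QALYs

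*Protocol article*

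**What the plan says.** The Main Outcomes section lists the PHQ symptom measures "as well as economical variables and EuroQol 5D outcomes in terms of QALYs". Symptoms, costs and QALYs therefore have equal standing.

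Missing data are addressed in two places.

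- **Analysis of Clinical Effectiveness.** The section opens with "This study will be conducted on an intention-to-treat basis". A repeated-measures ANOVA, "including all variables over time, will be performed to assess whether missing values respond to a random or non-random pattern", is the diagnostic step. The handling step is conditional: "If the missing values are greater than 5% the Expectation Maximization (EM) will be used as a data imputation method".
- **Cost-Utility Analysis.** The closing paragraph says "Missing-data analysis will be computed using Student’s *t*-test and chi-square tests". It continues: "Variables included in the analysis will be severity level, gender, and age"; and then "this will allow us to ascertain whether unexpected missing data due to participant dropout are related to chance or not". It names no imputation method, no analysis set and no consequence of the test results. The same section describes the bootstrap as "creating a large number of samples with replacement from the original sample data", with 1000 resamples.

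The sections describing the cost analysis and the ICER do not mention missing data. The Sensitivity Analysis section promises an analysis but does not say what it will vary.

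**The concern.** The economic comparison is the purpose of this sub-study, yet a handling rule for missing values appears only under the clinical heading. The economic section has a separate paragraph that stops at diagnosis.

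That diagnosis cannot do the work expected of it. A non-significant test does not establish that dropout is a matter of chance. A significant one shows only an association with a measured characteristic. Treatment arm, cost and EQ-5D are not among the listed variables, so the tests would not reveal dropout that differs by arm or depends on service use or quality of life.

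At stake are the incremental cost-utility ratio, the ICER and the bootstrap intervals. QALYs and total costs accumulate over follow-up, so one missed visit can leave a patient's total incomplete. Bootstrapping a selected sample gives an interval around the selected estimate and does not remove the selection.

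**Working it through.** The plan states no figure on this point that could be reproduced. The check sets the two procedures side by side, follows each possible reading, and then shows a range for the size.

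**Side by side**

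| | Clinical Effectiveness | Cost-Utility |
|---|---|---|
| Analysis population | Intention-to-treat, worded for the study | Not stated |
| Diagnostic step | Repeated-measures ANOVA | t-tests and chi-square tests on severity, gender, age |
| Handling step | EM if more than 5% missing | None stated |

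**Narrow reading: the EM rule covers clinical outcomes only.** Mean QALY and cost differences are then computed from whatever records are available. Once missing values exceed 5%, the ICER's effect comes from imputed data and its cost difference from observed cases, so one ratio can mix two populations.

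**Broad reading: the EM rule also covers costs and EQ-5D.** If EM is run once and the filled data set is then resampled, every resample treats the imputed values as observed. Uncertainty about those values is left out and the intervals are too narrow. The article does not state the order of imputation and resampling.

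**Size: complete records.** Inputs: 300 patients (Sample Size) and three follow-up assessments, namely post-treatment, 6 months and 12 months (Clinical Evaluation). The per-visit loss k is assumed.

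- Independent losses: share complete = (1 − k)³.
- Same patients missing every visit: share complete = 1 − k.

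| k | Independent | of 300 | Same patients | of 300 |
|---|---|---|---|---|
| 5% | 0.95³ = 0.857 | 257 | 0.95 | 285 |
| 10% | 0.90³ = 0.729 | 219 | 0.90 | 270 |
| 15% | 0.85³ = 0.614 | 184 | 0.85 | 255 |
| 20% | 0.80³ = 0.512 | 154 | 0.80 | 240 |

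**Size: possible bias on the narrow reading.** Suppose dropouts' mean QALYs are lower than completers' by g in both arms. The completer difference is then shifted by g × (dropout in TD-CBT − dropout in TAU). All inputs here are assumed.

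- 30% against 20% dropout: g = 0.02 gives 0.02 × 0.10 = 0.002 QALY; g = 0.10 gives 0.10 × 0.10 = 0.010.
- 40% against 20% dropout: 0.02 × 0.20 = 0.004; 0.10 × 0.20 = 0.020.
- Equal dropout: no shift under this model.

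**The case against.** The strongest reply is that the clinical section already covers the economic data. Its intention-to-treat sentence refers to the study as a whole, its ANOVA takes in all variables, and its EM rule speaks of missing values without naming the PHQ. The cost-utility paragraph could then be an extra diagnostic, compatible with EM imputation. This reading is possible. It does not explain why the economic section needs a different diagnostic of its own, and it leads to the single-imputation problem shown above.

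A reader might go further and infer that the main economic result defaults to completers, or that economic outcomes receive no method at all. The documents support neither. No section states a complete-case analysis. The mention of the original sample belongs to a general explanation of bootstrapping and does not define an analysis set. A missed visit also need not erase a patient's costs, because the Economic Assessment section draws on medical records as well as interviews. The Retention section adds emailed questionnaires, telephone prompts and continued follow-up of patients who leave treatment, although with emphasis on the first post-treatment assessment.

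Nor would it be right to say that at exactly 5% missing the symptoms are imputed and the costs are not. EM starts only above 5%, and that threshold concerns missing values, which is not the same as per-visit loss of patients.

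Finally, a condensed article may leave imputation detail to a fuller document. That would answer silence. Here the article states two procedures for outcomes of equal rank and does not relate them.

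**Conclusion.** The point holds as an unresolved difference between two stated procedures, with a weakness on either reading. On the narrow reading the cost-utility ratio rests on observed cases and the ICER may combine two populations. On the broad reading the intervals understate uncertainty, provided EM is run once before resampling. On both, the dropout tests lead to no action and cannot justify ignoring missing costs or EQ-5D values.

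The size cannot be fixed from the document, which gives no attrition figure. For assumed per-visit losses of 5% to 20%, complete records lie between 86% and 51% under independence and between 95% and 80% if the same patients miss every visit. These shares fit EQ-5D better than costs, where medical records may fill gaps. Bias on the narrow reading depends on dropout differing between arms, or on dropouts differing from completers to a different extent in each arm. The document does not show that either will occur.

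**What to change.** Replace the last paragraph of the Cost-Utility Analysis section with one rule for symptoms, EQ-5D and costs in all randomised patients:

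- Multiply impute by arm, at the level of visit-specific EQ-5D indices and cost totals. Suitable predictors are baseline EQ-5D, prior costs, PHQ scores, age, sex and centre.
- Combine the imputation with the planned 1000-sample bootstrap so that the intervals carry imputation uncertainty.
- Use the same patients in the numerator and denominator of both ratios.
- Under Sensitivity Analysis, name a complete-case analysis and one that shifts the imputed values, for example in the TD-CBT arm.
- Report dropout by arm descriptively, and do not let a significance test decide how missing data are handled.

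The clinical section should point to the same rule. The cost is wording, more computing and a somewhat longer methods description. Intervals will be somewhat wider than from a naive analysis. No new data or patients are needed.
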